## Methods/Design

### Study design

We will employ a cluster-randomised trial to allocate a condition (treatment vs. waiting list) at facility level. The project protocol has been approved by the ethical committees of Monash University and Southern Health.

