### Study protocol

The study period will be brief to reduce the likelihood that changes in outcomes are due to dementia progression, inter-current illness or other incidental events. Activity sessions must be long enough to detect changes in selected outcomes during the carer's visit, but not so long that sessions are likely to be interrupted by meals or nursing interventions. In our recently completed Montessori study [25], the choice of 30-minute sessions has worked well. A study period of up to four weeks has also proved feasible. We will therefore employ an exposure of six sessions spread over a three week period for both conditions. The choice of condition (treatment or control) will be randomly determined using Excel. The program from week 1 (W1) to week 5 (W5) is shown in Table 1. Baseline measures will be conducted at the start of the Montessori workshop or dementia education session (W1). All participants will receive a follow-up phone call half way through W2-W4 to ascertain they have filled out questionnaires after each visit. A face-to-face appointment will be made to complete the final measurements at the end of W4.

**Table 1 T1:** Program for treatment and control condition groups

	Treatment group	Control group
W1	Group Montessori workshop	Dementia education session

	↓	↓

W2 W3 W4	6 Montessori sessions	Waiting list period

		↓

W5		Group Montessori workshop

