### Recruitment

Aged care facilities will be contacted by telephone to explain the studies. If facilities show interest in the study, researchers will visit the facility to provide all relevant parties (director of nursing, nursing staff and diversional therapists) with more detailed information. If facilities consent to participate in the study, a pre-selection screening will be conducted to identify eligible participants. An appointed delegate of the facility will then contact the identified family carers to ask if they consent with forwarding their contact details to a Monash University researcher. When verbal consent is given a senior researcher will contact the carer to explain the study and answer queries. If carers express interest in the studies they will be sent a Participant Information and Consent Form package. Once written consent is received, researchers will gather baseline information and plan the training session with groups of up to six participants. If more than six family carers are eligible and interested in the study in a particular facility, more training sessions will be organised.

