### Sample size calculation

The sample size calculation is based on a study comparing wives caring for moderately impaired husbands that exhibit probable Alzheimer's disease with wives whose spouses demonstrate no mental or physical condition matched on sociodemographic background [34]. We calculated means per group (carers vs. non-carers) for the total Mutuality Scale of the Family Caregiving Inventory [28]. Caregiving wives reported a score of 2.89 and the control participants a score of 3.48 (pooled SD = 0.74), with higher scores indicating a higher quality of the relationship (effect size 0.80). We have used G*Power 3.1.2 (test family = t-test, statistical test = means: difference between two independent means (two groups), alpha = 0.05, power = 0.80 and effect size *d *= 0.80) to calculate that 21 participants in each condition would suffice to reveal such a difference. We estimate 20% attrition and will recruit 50 carers.

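### Facilities are randomised but the sample size treats carers as independent, so 50 carers do not give the stated 80% power at d = 0.80

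*Protocol article*

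**What the plan says.** Under Study design, the protocol article makes the facility the unit of allocation: "We will employ a cluster-randomised trial to allocate a condition (treatment vs. waiting list) at facility level".

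Under Sample size calculation, the unit is the carer. The means and SD come from a comparison of caregiving and non-caregiving wives on the Mutuality Scale: "Caregiving wives reported a score of 2.89 and the control participants a score of 3.48 (pooled SD = 0.74"), summarised as "effect size 0.80". The G*Power procedure is named as "statistical test = means: difference between two independent means (two groups"), with "alpha = 0.05, power = 0.80 and effect size" d = 0.80, and was used "to calculate that 21 participants in each condition would suffice to reveal such a difference". Attrition is put at 20% and the recruitment target at 50 carers. Whether alpha is one-sided or two-sided is not said.

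Under Recruitment, carers are trained within their facility in groups of up to six, and a facility may supply more than one group: "If more than six family carers are eligible and interested in the study in a particular facility, more training sessions will be organised".

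Under Statistical analysis, independent t-tests come first, and a multilevel model that includes the facility is the last step.

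**The concern.** The calculation assumes 42 independent observations. Carers in one facility share staff, surroundings and a training group, so their outcomes are likely to be correlated. Since the condition is constant within a facility, that correlation inflates the variance of the treatment contrast. A test that respects the allocation also has degrees of freedom set by the number of facilities, and these will be few with about 40 completers. Both effects lower power, and neither is in the calculation.

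This is not a detail left to a fuller document. The article gives the whole calculation, and it is the calculation for an individually randomised trial. If it stands, a null result will be read against 80% power that the design did not have.

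**Working it through.** **Inputs from the article.** Means 2.89 and 3.48, SD 0.74, alpha 0.05, target power 0.80, n = 21 per arm, attrition 20%, 50 carers recruited.

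**Inputs assumed, because the article gives none.** ICC 0.01, 0.05 and 0.10; either k = 5 facilities per arm with m = 4 completers each, or k = 4 with m = 5. Both give 20 completers per arm. Clusters are taken as equal in size.

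**Step 1: the plan's own figure.** d = (3.48 − 2.89)/0.74 = 0.797, rounded to 0.80. Power comes from the noncentral t distribution with noncentrality d√(n/2) and 2n − 2 degrees of freedom.
- n = 21: noncentrality 0.80 × √10.5 = 2.592, df 40. Power is 0.817 one-sided and 0.716 two-sided.
- A two-sided test would need 26 per arm.

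So 21 per arm is reproduced, but only with a one-sided test.

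**Step 2: attrition, still without clustering.** 50 × (1 − 0.20) = 40, or 20 per arm, two short of the required 42 in total. (Covering 42 would take 42/0.80 = 52.5, so 53 recruited.) Noncentrality is 0.80 × √10 = 2.530, df 38. Power is 0.799 one-sided and 0.693 two-sided. This is the baseline against which clustering has to be judged.

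**Step 3: add clustering.** Design effect DE = 1 + (m − 1) × ICC; noncentrality = 0.80 × √(20/(2 × DE)). Facility-level df = 2(k − 1), which is 8 for k = 5 and 6 for k = 4. Carer-level df stays at 38.

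| Layout per arm | ICC | DE | One-sided, carer df | One-sided, facility df | Two-sided, facility df |
|---|---|---|---|---|---|
| 5 facilities of 4 | 0.01 | 1.03 | 0.79 | 0.74 | 0.59 |
| 5 facilities of 4 | 0.05 | 1.15 | 0.75 | 0.69 | 0.55 |
| 5 facilities of 4 | 0.10 | 1.30 | 0.70 | 0.65 | 0.50 |
| 4 facilities of 5 | 0.01 | 1.04 | 0.79 | 0.71 | 0.55 |
| 4 facilities of 5 | 0.05 | 1.20 | 0.73 | 0.65 | 0.49 |
| 4 facilities of 5 | 0.10 | 1.40 | 0.68 | 0.60 | 0.44 |

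**Step 4: separate the sources.** For 5 facilities of 4 at ICC 0.05, one-sided:
- no clustering: 0.799
- design effect only: 0.749
- design effect and facility-level df: 0.694

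The correlation and the degrees of freedom each cost about five points.

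**Step 5: detectable difference at 80% power, facility-level df, ICC 0.05 and 0.10.**
- 5 facilities of 4: 0.92 and 0.98 SD one-sided; 1.09 and 1.15 SD two-sided.
- 4 facilities of 5: 0.98 and 1.06 SD one-sided; 1.17 and 1.26 SD two-sided.

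**The case against.** Several points on the other side have force.

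- **The size of the loss is assumed.** True. With a very small ICC and carer-level degrees of freedom the loss is slight (0.79 against 0.799 one-sided), and facility-level degrees of freedom are a conservative choice. But the starting point is already 0.799 on the most favourable reading, so any positive ICC leaves power below 0.80.
- **Attrition might be lower than planned.** With all 25 per arm completing, one-sided power on carer-level degrees of freedom stays at about 0.80 up to m = 6 and ICC 0.05. However, the plan itself expects 20% attrition.
- **The analysis does allow for facilities.** The final multilevel step deals with clustering in the analysis. It does not restore the power lost in the design.

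A reader might also infer more than the article supports.

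- **That the whole fall to about 0.50 is the cost of ignoring clustering.** It is not. The two-sided figures also carry the change from a one-sided to a two-sided test and the attrition shortfall, which alone bring power to 0.693. The like-for-like comparison is one-sided, from 0.80 to 0.69 or 0.65 for 5 facilities of 4 at ICC 0.05 and 0.10.
- **That two very large facilities per arm could supply the sample.** Allowing extra training sessions permits large clusters, but nothing says that the sample will come from so few facilities. A condensed article may also leave the number of facilities to the full protocol, so its absence alone is no fault.
- **That allocation is by unrestricted draws and may leave the arms lopsided.** The article says only: "The choice of condition (treatment or control) will be randomly determined using Excel". Excel can just as well produce a restricted list, so this wording does not show an imbalance risk.

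**Conclusion.** The point holds. The unit in the sample size calculation contradicts the unit of randomisation, and the stated 80% power at d = 0.80 is not delivered by 50 carers. That conclusion needs only a positive ICC or a test with facility-level degrees of freedom.

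The size is less certain than the direction. On the one-sided basis that the 21 implies, power is about 0.60 to 0.74 with 4 or 5 facilities per arm, facility-level degrees of freedom and ICC 0.01 to 0.10. If the test is meant to be two-sided, it is about 0.44 to 0.59, but part of that gap belongs to sidedness and attrition. These ranges depend on the assumed ICC, the number of facilities and equal cluster sizes.

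**What to change.** In Sample size calculation:
- State whether alpha is one-sided or two-sided.
- Give the planned number of facilities per arm and the expected completers per facility.
- Restate the power, or the detectable difference, for 40 completers using DE = 1 + (m − 1) × ICC over a stated ICC range (for example 0.01 to 0.10), with degrees of freedom based on the number of facilities.
- Remove the claim of 80% power at d = 0.80.

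This is a change of wording, and its only cost is a less favourable stated power.

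Keeping 80% power would need more facilities or more carers, which is a separate decision for the sponsor. As a guide, with m = 4 to 6 and ICC 0.01 to 0.10, DE runs from 1.03 to 1.50:
- One-sided: 21 × DE gives 22 to 32 per arm, so 55 to 80 recruited after dividing by 0.80.
- Two-sided: 26 × DE gives 27 to 39 per arm, so 68 to 98 recruited.

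These totals do not include the further allowance for few facility-level degrees of freedom.

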### Statistical analysis

We will use independent t-tests to compare the means of outcome measures for the Montessori and control conditions. Next, each outcome measure will be subjected to a 2-way ANOVA with condition (Montessori *vs*. control) as fixed factor. We will then undertake ANCOVAs to investigate whether the intervention enhances certain outcomes (e.g. quality of relationships) after controlling for others (e.g. quality of pre-morbid relationships) to explore the possibility of mediation. Secondly, we will extend these models to examine whether other factors, such as resident-carer relationship (e.g. spouse *vs*. child) and dementia severity (moderate *vs*. severe) serve to moderate treatment benefits. Finally, we will conduct a multilevel variant of these ANOVAs to include higher level factors such as the aged care facility.

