**Methods/Design:**

We will conduct a cluster-randomised trial to train family carers in conducting personalised one-to-one activities based on the Montessori methodology with their relatives. Montessori activities derive from the principles espoused by Maria Montessori and subsequent educational theorists to promote engagement in learning, namely task breakdown, guided repetition, progression in difficulty from simple to complex, and the careful matching of demands to levels of competence. Persons with dementia living in aged care facilities and frequently visiting family carers will be included in the study. Consented, willing participants will be randomly assigned by facility to a treatment condition using the Montessori approach or a control waiting list condition. We hypothesise that family carers conducting Montessori-based activities will experience improvements in quality of visits and overall relationship with the resident as well as higher self-rated mastery, fewer depressive symptoms, and a better quality of life than carers in the waiting list condition.

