### Outcomes measures

#### Primary measure

##### Quality of visits

We will ask carers to rate their overall satisfaction with each study visit on a 5-point Likert scale. In addition, they will complete a truncated version of the Pearlin Mastery Scale [26] adapted to care-related situations [27], focussing on their sense of personal mastery during each visit. Pioli (2010) [27] deleted two items of the original scale, because they were not specifically related to carer interactions: 'Sometimes I feel that I'm being pushed around in life' and 'What happens to me in the future mostly depends on me'. The remaining items will be reworded to make them relevant to visits, for example 'I had little control over the things that happened today when I spent time with my family member' and 'I felt helpless in dealing with the problems I experienced during my visit today'.

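### Facilities are randomised, but carer-level t-tests, ANOVAs and ANCOVAs come first, and nothing makes the final multilevel model the basis for the conclusion

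*Protocol article*

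**What the plan says.** The Study design section fixes the unit of randomisation: "We will employ a cluster-randomised trial to allocate a condition (treatment vs. waiting list) at facility level". The Methods/Design part of the abstract agrees: "Consented, willing participants will be randomly assigned by facility to a treatment condition".

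The Statistical analysis section then sets out a sequence:

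1. Carer-level tests: "We will use independent t-tests to compare the means of outcome measures for the Montessori and control conditions".
2. A second pass in which "each outcome measure will be subjected to a 2-way ANOVA with condition" as the fixed factor. It is called two-way, but no second factor is named.
3. Covariate models: "We will then undertake ANCOVAs to investigate whether the intervention enhances certain outcomes" after controlling for others, followed by moderator models.
4. Only then facility: "Finally, we will conduct a multilevel variant of these ANOVAs to include higher level factors such as the aged care facility".

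No step is named as the primary analysis. The Sample size calculation section also rests on an independent two-group t-test ("alpha = 0.05, power = 0.80 and effect size" *d* = 0.80), with no ICC and no design effect.

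**The concern.** An independent-samples t-test on carers is valid only if carers are independent given condition. Allocation by facility means that any facility effect falls wholly on one arm, and a carer-level standard error does not see it.

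The protocol gives reasons to expect such an effect. Training takes place in groups inside the relative's facility (Recruitment; Montessori-based activities). The Control condition section provides for the effect of carers meeting each other. Carers at one facility also share its environment.

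With several unranked models per outcome, a carer-level p-value could be reported as the result even where the multilevel model disagrees. Every treatment comparison is affected, including the primary measure.

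**Working it through.** **Inputs from the protocol.** Facility is the unit of randomisation. Alpha is 0.05, power 0.80 and *d* 0.80, with 21 carers per condition, 20% attrition and 50 recruited. The number of tails is not stated. Training groups hold up to six carers, with further sessions if more are eligible.

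**Assumptions, because the protocol gives no figure.** ICC from 0.01 to 0.20; 3–8 carers (*m*) in each of 3–7 facilities (*k*) per arm; equal cluster sizes; normal outcomes. The layouts used have 20–25 carers per arm. That matches 50 recruited (25 per arm) and 50 × 0.8 = 40 completing (20 per arm).

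**Step 1: the plan's own figure.** *d* = (3.48 − 2.89)/0.74 = 0.797, about 0.80. With noncentrality *d*·√(n/2), a one-sided t-test at 0.05 needs n = 21 per arm (power 0.817). A two-sided test needs 26, and 21 per arm then gives 0.716. So 21 reproduces, as a one-sided test on independent carers.

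**Step 2: size of the carer-level error, by formula.** Clustering multiplies the variance of the difference in means by DE = 1 + (*m* − 1) × ICC. The t-test leaves this out, so its two-sided rejection rate under the null is roughly 2[1 − Φ(1.96/√DE)]. For *m* = 6:

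- ICC 0.01: DE = 1.05, rate 5.6%
- ICC 0.05: DE = 1.25, rate 8.0%
- ICC 0.10: DE = 1.50, rate 11.0%
- ICC 0.20: DE = 2.00, rate 16.6%

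**Step 3: the same by simulation.** Null data, 40,000 replicates per cell, carer-level t-test at two-sided 5%:

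| Facilities per arm × carers | ICC 0.01 | 0.05 | 0.10 | 0.20 |
|---|---|---|---|---|
| 7 × 3 | 5.2% | 6.2% | 7.5% | 10.0% |
| 5 × 5 | 5.4% | 7.4% | 10.1% | 14.7% |
| 4 × 6 | 5.5% | 7.8% | 11.2% | 17.1% |
| 3 × 8 | 5.7% | 9.2% | 13.6% | 21.3% |

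Repeat runs move single cells by a few tenths of a point, and the top cell reaches about 22%. At ICC 0 the carer-level t-test is at about 5%. A t-test on facility means stays at about 5% in every cell.

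**Step 4: power of an analysis that respects the randomisation.** For a facility-mean t-test at *d* = 0.80, two-sided, the noncentrality is 0.80/√(2·DE/N), with N = *k* × *m* carers per arm and 2*k* − 2 degrees of freedom. Example, 5 × 4 at ICC 0.05: DE = 1.15, noncentrality 0.80/√(2 × 1.15/20) = 2.36, 8 degrees of freedom, power about 0.55. Across the layouts, power is about 0.56–0.70 at ICC 0 and 0.44–0.62 at ICC 0.05. Part of the gap from 0.80 is the two-sided convention. One-sided, the 4 × 6 layout gives 0.79 at ICC 0 and 0.71 at ICC 0.05.

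**The case against.** The strongest reply is that the remedy is already in the plan. A multilevel model with facility is promised, a simple-to-complex order of presentation is not an order of precedence, and a short article may leave the ranking of models to an analysis plan. The first part stands: this trial does not ignore clustering. But the article does not stay silent on analysis. It specifies carer-level tests as the first comparison of every outcome, and these do not match the randomised design. Nor can the unnamed second ANOVA factor be presumed to be facility, since the last step is described as the one that brings facility in.

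Four stronger readings are tempting, and the document does not support them:

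- *The t-tests are the declared headline result.* A reader might infer this from the order, but no analysis is named as primary.
- *The p-values are certainly too small.* That requires a positive ICC, and none is given. At ICC 0.01 the inflation is under one percentage point.
- *The six visit ratings per carer enter as separate observations.* The primary measure is collected per visit ("We will ask carers to rate their overall satisfaction with each study visit on a 5-point Likert scale"). Treating ratings as independent rows would give a false-positive rate of about 30–36%, with an assumed facility share of variance of 0.05 and carer share of 0.3–0.5. The plan does not state that analysis. One mean per carer is at least as natural a reading. The facility ICC of that mean would be 0.05/(0.05 + 0.3 + 0.65/6) = 0.11 or 0.05/(0.05 + 0.5 + 0.45/6) = 0.08, and the error about 8–10%.
- *Shared trainers cause the correlation.* The protocol says only that two researchers run each workshop. If the same pair serves all facilities, they add no between-facility variance.

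**Conclusion.** The point holds in conditional form. The carer-level t-tests, ANOVAs and ANCOVAs do not respect the randomised unit, and the one model that does comes last without being made the basis for inference. The inflation is negligible at ICC 0.01 and material from about ICC 0.05. Its size rests on the assumed ICC and layouts; 3 × 8 is the extreme and would need more than one training session per facility. This is a choice the text states, so it should be corrected before outcome data are analysed.

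**What to change.** Name the planned multilevel model as the primary analysis for each outcome:

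- condition as a fixed effect and a random facility intercept;
- a random carer intercept as well, if visit ratings are analysed individually and not as one mean per carer;
- a small-sample degrees-of-freedom correction (Kenward–Roger or Satterthwaite), because about 50 carers implies few facilities.

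Use a t-test on facility means as a check. Label the carer-level t-tests, ANOVAs and ANCOVAs as descriptive or unadjusted; they need not be deleted.

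**Cost.** The analysis change is one of wording and needs no new data, but it is not free. Confidence intervals widen and power falls below the stated 0.80 at the planned size. The Sample size calculation should restate power for the facility-adjusted analysis, giving the number of tails and the assumed ICC and carers per facility. A three-level model may be fragile with so few facilities, which favours one mean per carer for the visit ratings.

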#### Secondary measures

All of the following secondary measures will be completed at baseline and at the end of the three-week study period.

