##### Carer's mastery

Carers will complete five items of the Pearlin Mastery Scale matching the items administered at the end of every study visit but using the scale's original wording describing global mastery [26]. These items include, "I have little control over the things that happen to me" and "There is really no way I can solve some of the problems I have". This shortened scale has a high internal consistency with an *alpha *of 0.72 [27].

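### Every secondary outcome is scored at baseline, but no planned treatment comparison names the outcome's own baseline as a covariate

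*Protocol article*

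**What the plan says.** All references are to the protocol article.

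- **Data collected.** Under Secondary measures: "All of the following secondary measures will be completed at baseline and at the end of the three-week study period". This covers the relationship rating and Mutuality Scale, global mastery, CES-D and Carer-QoL.
- **First comparison.** Under Statistical analysis: "We will use independent t-tests to compare the means of outcome measures for the Montessori and control conditions". The text does not say whether these are end scores or change scores.
- **Second comparison.** "each outcome measure will be subjected to a 2-way ANOVA with condition" as the fixed factor. The label implies two factors, but only condition is named.
- **ANCOVAs.** These ask whether certain outcomes improve "after controlling for others (e.g. quality of pre-morbid relationships) to explore the possibility of mediation". The one example covariate, pre-morbid relationship quality, is listed under Other measures as collected at baseline.
- **Last step.** After the moderator models, "we will conduct a multilevel variant of these ANOVAs to include higher level factors such as the aged care facility". No baseline score is named here either.
- **Primary outcome.** Under Quality of visits: "We will ask carers to rate their overall satisfaction with each study visit on a 5-point Likert scale", together with reworded mastery items per visit. No pre-intervention value is described. The nearest baseline measure is the global mastery scale: "Carers will complete five items of the Pearlin Mastery Scale matching the items administered at the end of every study visit", though in the original global wording.

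**The concern.** In a trial this small, the outcome's own baseline is usually the most useful covariate available. It absorbs stable differences between carers, and it corrects for chance imbalance between arms, which allocation by facility makes larger. The section sets out its tests and their order in some detail, yet none of the steps puts that score to stated use.

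At stake is precision. The sample size rests on an unadjusted two-group t-test for the Mutuality Scale, which is one of the measures with a baseline. Any gain from adjustment therefore falls on the outcome used to size the trial.

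The mediation label is a second problem. Pre-morbid relationship quality precedes the intervention and cannot lie on the path from intervention to outcome. Controlling for it is baseline adjustment or, with an interaction, moderation.

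**Working it through.** **Inputs from the Sample size calculation section.** d = (3.48 − 2.89)/0.74 = 0.797, taken as 0.80; alpha 0.05; power 0.80; 21 per condition; 20% attrition; 50 recruited. Expected completers are 50 × 0.8 = 40, or 20 per arm.

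**Assumed.** The correlation r between baseline and end score is not in the document and is varied from 0.3 to 0.8. Baseline and end variances are taken as equal. Clustering is ignored until the last step.

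**Step 1: the plan's own figure.** For a two-sample t-test with noncentrality d√(n/2):

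- n = 21 gives 81.7% power one-sided and 71.6% two-sided. The stated 21 is therefore reproduced only with a one-sided test; two-sided, 26 per arm are needed. Sidedness is not stated.
- n = 20 completers per arm gives 69.3% two-sided.

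The trial has little precision to spare.

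**Step 2: variance of the arm difference**, with n per arm and outcome SD σ:

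- End score only: 2σ²/n
- Change score, which the condition-by-time test of a pre–post ANOVA equals: (2σ²/n) × 2(1 − r)
- ANCOVA on own baseline: (2σ²/n) × (1 − r²)

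The ratio of ANCOVA to end score is 1 − r². The ratio of ANCOVA to change score is (1 − r²)/[2(1 − r)] = (1 + r)/2. The sample multiplier is the inverse of the ratio.

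| r (assumed) | ANCOVA / end score | Multiplier | ANCOVA / change score | Multiplier |
|---|---|---|---|---|
| 0.3 | 0.91 | 1.10 | 0.65 | 1.54 |
| 0.5 | 0.75 | 1.33 | 0.75 | 1.33 |
| 0.6 | 0.64 | 1.56 | 0.80 | 1.25 |
| 0.7 | 0.51 | 1.96 | 0.85 | 1.18 |
| 0.8 | 0.36 | 2.78 | 0.90 | 1.11 |

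Both ratios are below 1 at every r shown, so ANCOVA is the more precise analysis whichever reading is right.

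**Step 3: what this means at 20 completers per arm**, d = 0.80, two-sided 0.05, noncentrality 0.80√(20/2)/√(1 − r²), 37 degrees of freedom:

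| Analysis | Power | Detectable d at 80% power |
|---|---|---|
| Unadjusted end score (38 df) | 69.3% | 0.91 |
| ANCOVA, r = 0.3 | 73.3% | 0.87 |
| ANCOVA, r = 0.5 | 81.2% | 0.79 |
| ANCOVA, r = 0.6 | 86.8% | 0.73 |
| ANCOVA, r = 0.7 | 93.2% | 0.65 |

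**Step 4: chance imbalance.** With 20 per arm the baseline difference between arms has standard error √(2/20) = 0.32 SD. An end-score comparison carries r times that imbalance into the estimate, for example 0.6 × 0.32 = 0.19 SD. This is another view of the same variance, not an additional loss.

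**Step 5: clustering.** With 6 carers per facility and an ICC of 0.05 (both assumed), the design effect is 1 + 5 × 0.05 = 1.25, so 40 completers are worth 40/1.25 = 32. The powers in step 3 are therefore upper figures for adjusted and unadjusted analyses alike.

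**The case against.** The strongest reply is that the text is incomplete rather than wrong, and that stronger readings go beyond it. A reader might infer four things that the document does not support.

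- **That baseline scores are discarded and the ANOVA merely repeats the t-test.** With condition alone F would equal t². But the text speaks only of outcome means, and a two-way label implies a second factor. Since the scales are measured twice, time is a natural candidate, and the condition-by-time test would use the baseline.
- **That the primary outcome loses its baseline too.** Visit ratings are collected per study visit and have none. Global mastery is at best a proxy for visit mastery, with unknown correlation, and it does not measure visit satisfaction.
- **That the ANCOVAs adjust only for other outcomes.** Their sole example is a baseline variable, so some baseline adjustment is planned, under the wrong label.
- **That imbalance is likely because there are few facilities.** The number of facilities is not stated. Training groups are capped at six carers, but a facility may hold several.

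It is also fair to say that covariate lists are often left to an analysis plan, that none is shown here, and that an unadjusted comparison is valid under randomisation.

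These replies limit the point without removing it. The section commits to named tests in a stated order and gives its covariates a stated purpose, so this is more than detail left for later. Even on the reading kindest to the plan, the condition-by-time test is less precise than ANCOVA at every correlation considered.

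**Conclusion.** The point holds for the secondary outcomes, as a loss of efficiency and not as bias. No treatment comparison names the outcome's own baseline, the second ANOVA factor is missing, and adjustment for a pre-intervention variable is described as mediation.

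For r from 0.5 to 0.7, the plan needs 1.33 to 1.96 times as many carers as baseline ANCOVA if end scores are compared, or 1.33 to 1.18 times if the unnamed factor is time. These figures assume equal variances and ignore clustering. Because r is assumed, the size of the gain is a range and not an estimate; its direction does not depend on r. The plan should be changed, since the remedy costs almost nothing and the expected two-sided power at 20 completers per arm is only 69.3% before clustering. No claim is made that the primary outcome loses a baseline score.

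**What to change.** 1. For the secondary outcomes, replace the t-test and two-way ANOVA steps with one main analysis: the multilevel model that includes facility, now planned last, with condition as fixed effect and the outcome's own baseline score as covariate.
2. If a two-way ANOVA is kept for any purpose, name its second factor and say which effect is the treatment test.
3. For the visit ratings, state in advance which baseline covariates enter the model. Global mastery may be named for visit mastery, acknowledged as a proxy.
4. Describe adjustment for pre-morbid relationship quality as baseline adjustment, and remove the mediation label from it.

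**Cost.** Wording in the analysis section and one degree of freedom per model for the added baseline score. The scores are already collected, so no new data, visits or participants are needed.
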